## 6 STUDY INTERVENTION(S) OR EXPERIMENTAL MANIPULATION(S)

### 6.1 STUDY INTERVENTION(S) OR EXPERIMENTAL MANIPULATION(S) ADMINISTRATION.

#### 6.1.1 STUDY INTERVENTION OR EXPERIMENTAL MANIPULATION DESCRIPTION

##### **Experimental and Control Arms:**

Program Delivery: Both experimental and control arm interventions involve 18 hours of curriculum, generally spread out over 3 to 6 week periods. The program is delivered with some variation in schedules to meet the needs of community partners and participating youth. Such configurations include but are not limited to: three 6-hour sessions spanning three weekdays during the summer (for job skills training only), nine 2-hour sessions held twice per week on weekday evenings, and six 3-hour sessions held once or twice per week on weekday evenings or Saturday afternoons (which was the preferred and most commonly used design).

Fidelity to intervention: For both intervention and control arms, research assistants are present at every session to track attendance, facilitate program implementation logistics (such as ordering food), and to complete detailed fidelity forms that assess facilitators' ability to deliver the content of the program as intended.

**Manhood 2.0 (experimental arm):** Manhood 2.0 guides youth to explore and reflect upon social constructions of masculinity, describe healthy relationships, discuss healthy sexual behaviors, identify coercive and disrespectful behaviors, and practice skills to intervene when witnessing peers' disrespectful and harmful behaviors, with repeated reflection on gender norms throughout these sessions. The curriculum involved three main topic areas. The first focuses on the theme of gender, masculinity and power, allowing the young men to actively reflect on the messages and expectations that they have received from society about manhood and gender norms. The second topic focuses on the theme of violence. This includes several components: an exploration of the various forms of violence, its impact on communities, and the role that masculinity may contribute; identifying healthy versus unhealthy romantic relationships; sexual consent and decision making; and bystander interventions when witnessing abusive behavior. The final topic area focuses on sexual and reproductive health, which includes providing

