#### 9.4.9 EXPLORATORY ANALYSES

We will also conduct two sets of exploratory analyses. First, we will conduct an intensity-adjusted analysis that reflects the actual delivery of the program. To achieve this, we will use a continuous score of “intensity” to replace the binary intervention variable in the models for the primary analysis. This score will be calculated for each round (program delivery) by using two sources of information. The first is information collected systematically about each session by trained research assistants who observed the sessions, including whether each task assigned to a module was performed (yes or no). The second is a summary measure of overall attendance for each round, tracked by using sign-in sheets with the research assistants. The second set will be a per-protocol analysis. This set of models will include only participants in the intervention arm that received the full intervention, defined as having covered a minimum threshold of tasks across the six sessions and having sufficient attendance. These measures replicate the intensity score values, but are then dichotomized to yes or no to receiving the full intervention. All control arm participants will be included in these models.

To explore whether demographics, youth pre-intervention risk and protective factors (e.g., history of SV/ARA exposure, sexual risk, connectedness), and site-level differences (e.g., staff experience, organizational capacity, intervention intensity) moderate the effect of the intervention on the primary and secondary outcomes, linear mixed models slightly different from those described above will be utilized. The outcome variables will be modeled as a function of the following variables: the outcome at baseline, the treatment group, the potential moderator, the interaction between the treatment group and moderator, and a random effect for cluster. A significant interaction suggests the presence of intervention effect heterogeneity, and we will follow the approach of Kraemer (53) by focusing on effect size derivation rather than formal hypothesis testing.

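### Section 9.4.9 lists intervention intensity, which is measured after allocation, as an effect moderator; its interaction with arm is either not estimable or not readable as effect moderation

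*Protocol*

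**What the plan says.** Section 9.4.9 of the protocol sets out to explore whether youth factors and "site-level differences (e.g., staff experience, organizational capacity, intervention intensity) moderate the effect of the intervention on the primary and secondary outcomes". Besides the outcome at baseline and the treatment group, the model contains "the potential moderator, the interaction between the treatment group and moderator, and a random effect for cluster". The planned reading is that "A significant interaction suggests the presence of intervention effect heterogeneity", to be followed up "by focusing on effect size derivation rather than formal hypothesis testing".

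The same section defines the intensity score: "This score will be calculated for each round (program delivery) by using two sources of information". One source is the research assistants' session records of whether each module task was carried out. The other is "a summary measure of overall attendance for each round, tracked by using sign-in sheets with the research assistants". In the intensity-adjusted analysis this continuous score takes the place of the binary arm variable.

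Section 6.1.1 says that "For both intervention and control arms, research assistants are present at every session to track attendance", and that fidelity forms are completed in both arms. It also describes two different curricula: Manhood 2.0 in one arm, and six job-skills modules in the other. No section says what intensity value a control round receives in the moderation model.

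**The concern.** A moderator of a randomised effect should be a characteristic that the allocation cannot have changed. Intensity does not qualify. It exists only once a cluster has been allocated and its program has run, and the way it is built depends on which program that was. Section 6.2.1 adds that fidelity and feedback forms are used to correct delivery while the program is running, so the score also reflects management of the allocated program.

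Section 9.4.9 is inconsistent on this. The same score is the exposure in one analysis and a modifier of that exposure in another. In the sentence that lists it as a moderator, the youth risk and protective factors are limited to those present before the intervention. Aim 3 (Sections 4.1 and 9.1) gives only staff experience and organizational capacity as setting-level examples, although that list is illustrative.

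At stake is how a result would be reported. A non-null interaction with intensity would be labelled effect heterogeneity, when it may reflect only which sites or rounds managed to deliver a program and keep attendance up. Randomisation does not protect that contrast.

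**Working it through.** The protocol gives no figure for this analysis, so there is none to reproduce. Two checks apply.

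**1. Can the interaction be estimated?**

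Inputs: 11 experimental and 10 control clusters (Section 6.3); fixed-effect terms from Section 9.4.9. Write A for arm (1 = Manhood 2.0, 0 = control) and I for intensity. The columns of interest are 1, A, I and A×I. The baseline outcome is left out because it does not affect the argument.

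- *Control rounds coded 0.* In the experimental arm A = 1, so A×I = I. In the control arm I = 0, so A×I = 0 = I. The two columns are identical in every row, whether rows are clusters, rounds or participants. With 11 + 10 clusters the matrix has 4 columns and rank 3. If one redundant column is dropped, the surviving slope is a non-randomised association of delivery with outcome inside the Manhood 2.0 arm.
- *Control rounds scored on job-skills delivery.* The rank is 4 and the interaction can be estimated. It compares the slope of outcome on Manhood 2.0 delivery with the slope of outcome on job-skills delivery.

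**2. Under the second coding, can the interaction be non-null with no effect at all?**

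The values below are assumptions chosen to illustrate; none is in the protocol. An unmeasured site factor U (SD 1) drives both delivery and outcome:

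- outcome: Y = −0.3·U + error, error SD 0.3, with no arm effect and no intensity effect;
- intensity: I = b·U + error, error SD 1, with b = 1 in the experimental arm and b = 0, 0.5 or 1 in control.

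The large-sample slope of Y on I within an arm is cov(Y, I)/var(I) = −0.3·b/(b² + 1). The interaction is the experimental slope minus the control slope.

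- Experimental, b = 1: −0.3/2 = −0.150.
- Control, b = 0: 0. Interaction −0.150.
- Control, b = 0.5: −0.15/1.25 = −0.120. Interaction −0.030.
- Control, b = 1: −0.150. Interaction 0.

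Simulation agrees, with interaction coefficients of −0.150, −0.030 and 0.001. With 11 versus 10 clusters and a two-sided 5% t test on 21 − 4 = 17 degrees of freedom, rejection rates were 14.8%, 6.5% and 5.2%.

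The interaction vanishes when the two within-arm slopes coincide, as they do when delivery tracks the site factor equally in both arms. Nothing in the protocol secures that, and the two programs differ in content. In the equal case the intensity slope is still about −0.15 in each arm although intensity has no effect, so any intensity coefficient needs a non-randomised label.

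**The case against.** The strongest reply has four parts.

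- *Control scoring is not stated.* A reader might infer that the protocol scores each arm on its own curriculum. It does not say so. Section 6.1.1 shows only that the data exist in both arms. Using the score in place of the arm variable, and applying the full-intervention threshold only to the intervention arm, could equally suggest a dose scale with controls as reference. This stands: the different-curriculum problem is conditional. The alternative coding does not rescue the analysis, because the interaction is then not estimable. A statistical analysis plan could settle the coding, but neither of these two codings makes intensity a pre-allocation feature.
- *The result is not meaningless.* A reader might infer that the interaction has no valid interpretation of any kind. That is too strong. It cannot be read as effect moderation, but an association between delivery and outcome can still be described, for example within the Manhood 2.0 arm.
- *The analysis is exploratory and estimates effect sizes.* This stands as a limit on importance. It does not cure the problem, because the effect size itself is what is confounded: in the illustration the coefficient was −0.150 with no true effect.
- *Harm is not demonstrated.* This stands. The protocol does not say it would claim that the program works when delivered well, and that well-attended rounds differ in risk or motivation is plausible but not documented. Task completion is also recorded delivery by facilitators rather than participants' reception of the program, although it too arises after allocation.

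**Conclusion.** The point holds in a limited form. Intensity is measured after allocation, doubles as the exposure in the same section, and is listed as a moderator whose interaction is to be read as effect heterogeneity. With controls coded 0, that interaction cannot be estimated. With controls scored on job-skills delivery, it compares two different quantities and mixes any effect with whatever drives delivery. The conclusion rests on the stated construction of the score and does not depend on the simulation's assumed values.

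Size and direction of bias cannot be computed, because the protocol gives no distribution of intensity or attendance; the simulated rates show only that a spurious interaction is possible. The importance is low: no primary or secondary conclusion depends on this item, and the intention-to-treat comparison is untouched.

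**What to change.** - In Section 9.4.9, delete intervention intensity from the site-level moderator examples and state that site-level moderators are limited to features measured before allocation. Staff experience and organizational capacity stay if they refer to the site at entry. Facilitator training began differently in the two programs (Section 6.2.1), so say which staff are meant.
- Keep intensity in the intensity-adjusted analysis already planned, and report it there as a non-randomised, descriptive dose association.
- Section 9.4.1 plans to compare intervention effects between sites by how engaged staff and facilitators were in delivering the curriculum. That is also a delivery measure and should be treated the same way.

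The cost is a few words in two sections. One exploratory look at delivery-related variation in effect is given up; the intensity-adjusted analysis does not replace it, since there the score stands in for arm and is not crossed with it. No new data are needed for the deletion.

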### Primary Outcome:

**SV/ARA perpetration:** At baseline and T3 (9 months post-intervention), participants report whether they perpetrated the following SV or ARA behaviors in the last 9 months. The primary outcome measure for the study is any report of SV or ARA perpetration, i.e., yes to any of the following items.

The following two constructs focus on ARA behaviors against a dating partner. "Any ARA perpetration" is measured as a yes to any of these 13 items.

**Physical/Sexual relationship violence:** Three items are used to assess physical or sexual violence perpetration against a partner or ex-partner.(33) Participants report whether they performed each action, which is dichotomized as yes to any. Examples include "hit, pushed, slapped, choked or otherwise physically hurt someone you were going out with or hooking up with?" and "used physical force or threats to make someone you were going out with or hooking up with have sex (vaginal, oral, or anal sex) when they didn't want to?"

**Dating abuse:** A ten-item scale, developed for use with high school-aged students, is used to assess whether the participant perpetrated any abuse against a dating partner (34). Examples include "convinced them to have sex, after they said no a few times" and "told them not to talk to others or told them who they could hang out with." A positive response to any of these items is counted as any ARA perpetration.

"Any SV perpetration" is measured as yes to any of the sexual relationship violence and dating abuse items above as well as yes to any of the behaviors below.

**Non-partner sexual violence:** To measure whether a participant committed sexual violence against a *non-partner*, the two sexual IPV items were modified to query for people they had NOT gone out with or hooked up with, and included friends, family, and strangers (33). Responses are dichotomized as yes to any.

**Incapacitated sex:** Participants are asked if they had done something sexual with someone when that person was "too drunk or high to stop you,"(35) with a response of "yes" coded as yes to incapacitated sex.

**Use of drugs or alcohol on purpose for sex:** Participants are asked whether they had purposely given someone alcohol or drugs to do something sexual with that person(36). A response of "yes" is coded as yes to use of drugs or alcohol on purpose for sex.

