## 9.4 STATISTICAL ANALYSES

### 9.4.1 GENERAL APPROACH

Generalized linear mixed models will be used to account for the correlation among youth from the same cluster as well as the correlation between observations from the same youth. Descriptive statistics will be used to summarize the sample with regard to baseline characteristics of interest. Means and standard deviations will be presented for continuous variables, while sample proportions will be provided for categorical variables. 95% confidence intervals will accompany all sample statistics. Primary assessment of intervention effects will be based on intent-to-treat estimates. As-treated, or treatment-on-the-treated (TOT), effect parameters will be estimated in secondary analyses and reported as exploratory. Between-site differences regarding intervention effects will be assessed based on level of staff/facilitator engagement in curricular delivery as well as other observed external factors that may interact with the intervention to alter outcomes. SAS software will be used for all statistical analyses.

To assess differences at baseline between the youth in the experimental and control groups, demographics such as grade-level, race, nativity, and parental education will be compared while accounting for within-neighborhood clustering. Demographic variables as well as neighborhood-level characteristics resulting in between-arm imbalances will be considered as covariates in the primary and secondary analyses.

Participation bias will be assessed by comparison of age and race/ethnicity of youth participating in the study compared to the overall demographics of adolescents (school district and census data). Significant differences detected via chi-square analysis will be noted as potential validity threats.

An attrition analysis will be conducted by comparing youth who completed follow-up surveys with those who did not with regard to demographics as well as outcomes measured at baseline. All hypotheses will be two-sided tests with a significance level of 5%.

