#### 9.4.2 ANALYSIS OF THE PRIMARY ENDPOINT(S)

The primary outcome for this study is reductions in self-reported perpetration of SV and ARA at Time 3, compared to controls. We will examine whether Manhood 2.0 results in improvements in the primary outcome assessed at 9 months after end of program (Time 3) compared to controls. Generalized linear mixed models will be used and will include variables for baseline SV/ARA perpetration, treatment group, and random effects for cluster.

---

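### Section 9.4.9 names a linear mixed model for moderation of the yes/no primary outcome, which gives wrong interaction standard errors when subgroup risks differ and changes the effect scale without saying so

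*Protocol*

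**What the plan says.** Protocol 8.1 defines a binary primary outcome: "The primary outcome measure for the study is any report of SV or ARA perpetration". Protocol 9.4.2 analyses it accordingly: "Generalized linear mixed models will be used and will include variables for baseline SV/ARA perpetration, treatment group, and random effects for cluster". The general approach in 9.4.1 also names generalized linear mixed models.

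Protocol 9.4.9 asks whether demographics, youth risk and protective factors and site-level differences "moderate the effect of the intervention on the primary and secondary outcomes". For this, "linear mixed models slightly different from those described above will be utilized". The listed terms are "the outcome at baseline, the treatment group, the potential moderator, the interaction between the treatment group and moderator, and a random effect for cluster". The result is read as follows: "A significant interaction suggests the presence of intervention effect heterogeneity". The same sentence then says the approach will be one of "focusing on effect size derivation rather than formal hypothesis testing". The general rule in 9.4.1 is "All hypotheses will be two-sided tests with a significance level of 5"%.

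The protocol states no error rate for the interaction and no association between any moderator and perpetration.

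**The concern.** Read literally, 9.4.9 fits an identity-link model with one residual variance to a yes/no outcome. Two things follow.

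1. **Standard errors.** The variance of a binary outcome is p(1-p), so it differs between subgroups that differ in risk. A common residual variance misstates the standard error of the arm-by-moderator term even when the program does nothing for anyone. This fault does not depend on the preferred effect scale.
2. **Scale.** An interaction in a linear model is a difference in risk differences. A program effect with one odds ratio throughout gives different risk differences where base risks differ, and so appears as an interaction. The text does not announce this change of scale.

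The condition that triggers both is one the protocol leads one to expect. Section 2.1 ties unhealthy sexual behavior to perpetration, section 2.2 names several individual and contextual correlates, and sexual risk and prior SV/ARA exposure are among the planned moderators. Aim 3 asks where outcomes differ, so subgroup effects and their precision are what it delivers.

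**Working it through.** There is no stated figure for this analysis to reproduce, so the check derives the behavior of the test.

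**Inputs from the protocol (4.1, 9.2).** 866 participants, 80% retention, 21 clusters (11 and 10), ICC 0.01, 20% control rate, and an 8.3-point reduction, i.e. to 11.7%. Analysed: 866 x 0.80 = 693, or 33 per cluster and 346.5 per arm. Implied odds ratio: (0.117/0.883)/(0.20/0.80) = 0.53.

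**Assumptions, not in the protocol.** An individual-level binary moderator; q = share of youth in the higher-risk subgroup; p0 and p1 = risks in the lower- and higher-risk subgroups, chosen so that the overall rate is about 20%.

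**Step 1: no program effect, closed form** (clustering and baseline adjustment ignored). Let v0 = p0(1-p0), v1 = p1(1-p1), n per arm.

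- True variance of the interaction: (2/n)[v0/(1-q) + v1/q].
- Variance the linear model reports: (2/n)[(1-q)v0 + q v1][1/(1-q) + 1/q].
- Ratio: R = [q v0 + (1-q) v1] / [(1-q) v0 + q v1]; n cancels.
- Actual rejection at nominal 5%: 2Φ(-1.96/√R).

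Example, q = 0.20, p0 = 13%, p1 = 48%: v0 = 0.1131, v1 = 0.2496; R = 0.2223/0.1404 = 1.583; √R = 1.26; rejection 2Φ(-1.558) = 11.9%. A nominal 95% interval then covers about 88%.

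| q | p0 | p1 | odds ratio | √R | closed form | simulated |
|---|---|---|---|---|---|---|
| 10% | 16.5% | 52% | 5.5 | 1.27 | 12.1% | 12% |
| 15% | 15% | 48% | 5.2 | 1.26 | 12.0% | 10.5% |
| 20% | 13% | 48% | 6.2 | 1.26 | 11.9% | 12% |
| 20% | 15% | 40% | 3.8 | 1.20 | 10.4% | 9-10% |
| 30% | 12% | 39% | 4.7 | 1.17 | 9.3% | 9-10% |
| 30% | 17% | 27% | 1.8 | 1.07 | 6.7% | not run |
| 50% | any | any | any | 1.00 | 5.0% | 5% |
| 70% | 7.8% | 25.2% | 4.0 | 0.83 | 1.9% | not run |

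The simulated column uses 21 clusters of 33, ICC about 0.01, a random-intercept linear model with the 9.4.9 terms, and 2,000 trials per setting. A separate simulation of 1,500 trials per setting, again with no program effect, gave 10.7% (q = 20%, odds ratio 4), 10.5% (q = 30%, odds ratio 6) and 4.4% (q = 50%, odds ratio 4). Logistic interaction tests on the same data rejected 3.7-5.0%.

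**Step 2: change of scale.** Apply the odds ratio 0.53 to both subgroups of the worked example:

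- 13% falls to 7.3%, a difference of 5.7 points.
- 48% falls to 32.9%, a difference of 15.1 points.

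The linear model sees an interaction of about 9.5 points before baseline adjustment. Its rejection rate under a constant odds ratio of 0.53 follows the assumed moderator odds ratio (q from 20% to 50%): 5.7-6.2% at 1, 9.5-11.7% at 2, 22-26% at 4 and 29-32% at 6. With a weaker program effect (odds ratio 0.75) it is 8-14% for moderator odds ratios of 2 to 6. The logistic test stays at 3.7-6.1% under the constant odds ratio of 0.53.

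**Step 3: the reverse case.** Take 8.3 points off both subgroups instead:

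- 13% to 4.7% is an odds ratio of (0.047/0.953)/(0.13/0.87) = 0.33.
- 48% to 39.7% is an odds ratio of (0.397/0.603)/(0.48/0.52) = 0.71.

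Here the linear model has no interaction and the logistic model does. In simulation the logistic test rejects up to about 47% under such a constant reduction.

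**The case against.** The strongest reply is that this is loose wording. The models above 9.4.9 are generalized linear mixed models, the new ones are called only slightly different, and the next sentence supplies the difference: a moderator and its interaction with arm. That reading is plausible. It does not remove the point, because an analyst who follows the words would fit the linear model, and correcting the words costs almost nothing.

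Second, a linear model is not inherently unsound here. Section 9.4.9 does not specify the standard error. With subgroup-specific variances on the risk-difference scale, rejection returns to about 5-6%. This stands: Step 1 concerns the common-variance model that the text describes by default.

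Third, a reader might infer from Step 2 that the planned test raises false alarms at two to six times its nominal level. The documents do not support that. Section 9.4.2 states no link, and 9.2 expresses the planned effect as an absolute and a relative reduction, so a constant odds ratio is not the protocol's declared null. Most of the excess in Step 2 is a real difference in risk differences, and Step 3 shows the logistic test doing the same in the opposite case. The larger rates also need moderator odds ratios of about 4 to 6, and the protocol gives none.

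Fourth, the analysis is exploratory and stresses effect sizes over testing. This limits the consequence but does not dispose of it: effect sizes and any intervals come from the same model, and 9.4.9 still reads a significant interaction as heterogeneity.

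**Conclusion.** The point holds in a limited form. As written, 9.4.9 applies a linear mixed model to a binary outcome that 9.4.2 handles with a generalized linear mixed model.

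- **Fault independent of scale.** With no program effect, a nominal 5% interaction test rejects about 7-12% when the higher-risk subgroup is a minority, about 5% with equal subgroups, and below 5% (about 2% in the example) when it is the majority. This assumes a common residual variance, an individual-level binary moderator, an overall rate near 20% and moderator odds ratios of about 1.8 to 6. An unrelated moderator does no harm.
- **Unstated change of scale.** A constant odds ratio would show up as an interaction. That is a change of estimand and not a pure false positive, and its size depends on a moderator-outcome association that the protocol does not give.

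The primary conclusion is untouched. What is affected is the reliability of the subgroup findings under Aim 3. The correction should be made.

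**What to change.** In 9.4.9:

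1. For the binary primary outcome, use the generalized linear mixed model of 9.4.2, with the same link, baseline term and cluster effect, plus the moderator and the arm-by-moderator term.
2. Keep linear mixed models for the mean-score outcomes.
3. State the scale on which heterogeneity of the primary outcome is judged.
4. Report each subgroup's program effect as both an odds ratio and a risk difference, with 95% confidence intervals. A reader can then see whether an interaction exists on one scale only.

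The cost is a few sentences of analysis text. No new data are needed, and the model family is the one already planned for the primary analysis. The one drawback is that the model may converge less easily in rare subgroups.
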